#### Implementation determinants

Hypotheses H1, H2, and H4 will be tested using measures of implementation determinants. The 10-item version of Organizational Readiness for Implementing Change (ORIC) will be used to determine a collective level of organizational readiness for change [37]. The scale measures how well employees at an organization feel they can implement the change in processes required by a proposed intervention and the degree to which they are likely to initiate change, exert greater effort, exhibit greater persistence, and display more cooperative behavior. The measure consists of two subscales labeled Change Commitment (5 items) and Change Efficacy (5 items). Items are measured on a 5-point Likert scale from 1 (disagree) to 5 (agree). Sum score is calculated across all items. Lower scores represent less organizational readiness for implementing change; higher scores represent a more favorable organizational readiness for implementing change.

To measure other implementation determinants, we will use Implementation Determinants Measure (IDM). It consists of 47 items assessing factors that may hinder or foster successful implementation of an intervention into a given context. The measure is based on a 40-item scale, which was partly founded on CFIR [30] and partly on qualitative interviews with people involved in implementing mental health promotion programs in schools and kindergartens in Norway [32–34]. For the present study, IDM was adapted and customized to fit SPARCK and the municipal services in Norway, as well as the current study’s target problem areas. The measure includes seven items not included in the 40-item version. The adaptations and additional items cover findings gained from the semi-structured interviews with 14 SPARCK practitioners and 15 municipal leaders who used SPARCK in the two test cycles [19, 27]. Additionally, they cover items from pilot tests of the adapted version among relevant municipal practitioners and leaders. Three of the seven additional items came about after splitting the original items. Item 1a is “*The training in the innovation was of good quality*” and 1b “*The supervision of the innovation practitioners is carried out often enough*.” The original item combined training and supervision and quality and frequency in one item, which did not fit our intervention. Item 13 is split into three items, from the original one to cover three distinct target problem areas (prevention of development of anxiety, depression, and behavioral problems). As an example, item 13a reads “*There is a need for innovations that prevent the development of anxiety in children in Norwegian municipalities today*.” Pilot testing revealed a missing area in the measure’s content, leading to the addition of the following item to address it: 41 “*The innovation is appealing to our collaborating partners (i.e., other municipal services, out-patient clinics)*.” The pilot test and results from the prior qualitative implementation study [27] led us to add three more items, namely item 42 “*The ways of working with the innovation is compatible with existing clinical practice*,” item 43 “*We have the needed resources to work with the new innovation (staff, money, time, supplies, *etc*.)*,” and item 44 “*The innovation can easily be adapted to fit each family’s problem area and needs*.” Importantly, we made an effort to reflect the updated CFIR 2.0 [31] and an abbreviated measure of the CFIR-based Barrier Buster Tool when modifying and adapting it. The latter, developed by the CFIR Research Team in Ann Arbor, MI (based on unpublished work), assesses the constructs most reported to be associated with implementation outcomes. The final 47-item measure covers the CFIR domains innovation (14 items), outer setting (4 items), inner setting (8 items), individuals (8 items), and implementation process (13 items). Together, these comprise several sub-constructs (i.e., innovation relative advantage, innovation complexity, individuals’ attitudes, skills and motivation, external pressure, tension for change, implementation climate, available resources). Items are measured on a 7-point Likert scale from 1 (strongly disagree) to 7 (strongly agree). After reversing negatively phrased questions, a sum score will be calculated across all items. Lower scores indicate less positive environment for successful implementation; higher scores indicate more positive environment for successful implementation. In addition, one open ended question is included (“*Can you think of other factors that may affect the effectiveness or implementation of the intervention (positively or negatively)?*”). After the study period, the IDM will also be used to detect barriers within and across organizations and municipalities, to guide selection and/or tailoring of relevant implementation strategies if SPARCK is implemented and scaled up. Subsequently, data from the IDM will be used in a future study to identify and understand relations between implementation strategies and mechanisms of change [49].

#### Implementation strategies

Implementation strategies used during the clinical testing of SPARCK will be specified and reported throughout the study period (see Additional file 1 for a list of initiated and planned implementation strategies), along with reporting of and justification for tailoring of strategies. Strategies will be named and defined to align with the Expert Recommendations for Implementing Change (ERIC) compilation [25] and Proctor et al.’s [39] recommendations for specifying and reporting implementation strategies. Choice and adaptation of implementation strategies are based on NUBU’s implementation infrastructure and experience with implementing other EBIs [45], relevant implementation theories, models, and frameworks [26, 30, 31, 38], as well as data from the contextual analysis of barriers and facilitators to implementation in the development and optimization phase of the SPARCK project [27]. After study completion—and if SPARCK will be implemented into regular practice, there will be a follow-up study in which stakeholders will be asked to aid in choice and tailoring of appropriate implementation strategies to address barriers and facilitators, as well as investigation of implementation mechanisms [49].

### Data analysis

In implementation science, it is well-established that the contexts in which EBIs are implemented are inherently multilevel and interconnected [18]. Despite the recognized complexity, multilevel methods remain underutilized in implementation studies [50]. In our study, there are hierarchical structures that need to be either accounted for or modeled. For instance, families are nested within practitioners and leaders who in turn are nested within municipalities, and for some of the outcomes multiple responses over time are nested within individuals (i.e., practitioners and leaders). Given this longitudinal and hierarchical structure of our data, we will use multilevel models (MLM). In general, we will conduct multilevel regression analyses to investigate relations between predictors and outcome variables. However, despite the multilevel structure of the data, we do not expect nesting at all possible levels to be relevant. Thus, investigation of intraclass correlation coefficients (ICC) and design effects will guide our decisions regarding modeling [51].

More specifically, in H1, which concerns implementation determinants as predictors of implementation outcomes, we will regress implementation outcomes at T2 on implementation determinants at T1. In essence, this means a potential two-level model (practitioners/leaders are nested within municipalities). To investigate H2, concerning a relation between implementation determinants and parent reported clinical outcomes, estimates of change from pre to post or pre to follow-up [21] in child symptoms will be regressed upon either a mean-variable of practitioner/leader reported implementation determinants at T1, T2, and T3, or practitioner/leader reported implementation outcomes as a time-varying covariate (predictor). The same strategy will be used to investigate H3, only with implementation outcomes as predictor. In these analyses, there are potentially three levels (families nested within practitioner/leader which are nested in municipalities). Importantly though, we aim towards a parsimonious model in which complexity in the model is introduced only if the first steps in the model suggest it is necessary (e.g., through high ICC and design effects). To investigate H4, concerning a positive development in ratings of implementation determinants and outcomes over time, a multilevel growth curve model with three levels (repeated measures [level 1], nested within practitioners/leaders [level 2], nested within municipalities [level 3]) could be a solution given the nesting in our data. However, as we have a small sample size and data over time is gathered with one year in between, we will consider a less complex model [52]. Across all analyses, model building will be conducted in a stepwise fashion and improvement will be assessed for each step [53, 54] through model comparisons using -2LL, AIC, and BIC. Thus, maximum likelihood estimation is used for model comparisons and restricted maximum likelihood for final parameter estimates. Missing data will be handled using full information maximum likelihood, in which all available data in the model contribute to the parameters in the final model [55]. Although we have not specified specific mediator and moderator analyses in the present protocol study, we will explore potential theoretically and empirically relevant mediators and moderators in cross-level mediation and interactions models. Finally, we will explore differences between municipalities involved in the optimization process and those not involved, to assess whether co-creation is associated with implementation outcomes.

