## Methods

### Aim

This study is part of a larger effectiveness-implementation trial of the parent training intervention SPARCK. In a randomized controlled trial (RCT), SPARCK’s clinical effectiveness in preventing and reducing negative outcomes and promoting positive outcomes in children and parents is investigated. A separate study protocol is written for the RCT [21]. In order to grant appropriate attention and space to the implementation part of the project, a separate implementation study protocol was deemed warranted. In the current study, we aim to investigate the relations between implementation determinants [30, 31] and successful implementation of SPARCK, measured by four key implementation outcomes, namely fidelity, acceptability, appropriateness, and feasibility [5]. In addition, we examine how implementation determinants and implementation outcomes are associated with clinical outcomes of the intervention. More specifically, we have four research hypotheses to guide investigation of the implementation of SPARCK: (H1) positive ratings of implementation determinants are associated with better implementation outcomes; (H2) positive ratings of implementation determinants are associated with better clinical outcomes for parent and child; (H3) better implementation outcomes are associated with better clinical outcomes for parent and child; (H4) implementation determinants and outcomes are rated more positively with increasing experience with SPARCK (i.e., over time). For this last hypothesis, we will also investigate the bi-directional relations between implementation determinants and implementation outcomes over time.

In addition to these hypotheses, we will explore whether practitioners and leaders from the municipalities that engaged in the co-creation process of SPARCK report higher initial levels of organizational readiness than those from municipalities recruited directly to the combined RCT and implementation study. Finally, the implementation strategies ultimately used, modified, added, or omitted in the trial will be specified and reported in a separate article [25, 39]. Collectively, these efforts may lead to improved clinical outcomes when SPARCK is implemented in clinical settings, along with better contextual fit, greater implementation success, and a reduced time lag between research findings and their application in practice [18, 43, 44].

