### Study design and data collection

This study is a correlational implementation study performed alongside a two-armed RCT [21]. The combined study can be described as a hybrid effectiveness-implementation type 2 trial [43, 44], although the implementation strategies are not tested per se. To test the four research hypotheses, we will include a quantitative longitudinal web-based data collection spanning three time points, among SPARCK practitioners and their leaders. The first time point (T1) was during the initiation of the intervention in 2023, shortly after training of practitioners and information dissemination to leaders. The second data collection (T2) was after approximately 1 year when the practitioners had completed two cases each. The last data collection (T3) will be conducted after approximately 2 years (2025), when the practitioners have completed four cases each. In addition, for hypotheses H2 and H3 concerning relations with clinical outcomes, we will also include parent reported data on child symptoms and parent–child interaction from the RCT at pre, post (treatment termination), and follow-up (6 months after post) [21].

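### Under the three-wave mean option, H2 and the survey-based part of H3 predict a family's outcome partly from ratings given after that family's treatment has ended

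*Protocol article*

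**What the plan says.** The Data analysis section of the protocol article sets out H2 as follows: "estimates of change from pre to post or pre to follow-up [21] in child symptoms will be regressed upon" one of two predictors. The first is "a mean-variable of practitioner/leader reported implementation determinants at T1, T2, and T3". The second is introduced by "or practitioner/leader reported implementation outcomes as a time-varying covariate (predictor"). For H3 the text adds: "The same strategy will be used to investigate H3, only with implementation outcomes as predictor".

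Study design and data collection fixes the timing of the ratings. For T1: "The first time point (T1) was during the initiation of the intervention in 2023, shortly after training of practitioners". T2 was "after approximately 1 year when the practitioners had completed two cases each". T3 is planned for about two years, "when the practitioners have completed four cases each". Clinical outcomes are taken per family before treatment, at treatment termination, and six months later.

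Three other statements bear on the point:

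- H1, in the same section, keeps time order: outcomes at T2 are regressed on determinants at T1.
- H4 (Aim) expects that "implementation determinants and outcomes are rated more positively with increasing experience with SPARCK". Bi-directional relations are considered there, but only between determinants and implementation outcomes.
- The fidelity questionnaire (FidQ) is completed after each session, so most of it is recorded while the family is in treatment (Implementation outcomes).

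**The concern.** A predictor is normally measured before what it predicts. Here part of the averaged rating is given once the practitioner already knows how the family fared. Staff whose families improved may then rate the intervention, or the conditions for using it, more favourably. The clinical result would feed into the predictor, and the association would lean in the hypothesised direction without any influence of ratings on families.

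What is at stake is the interpretation. The Data analysis section calls these ratings predictors, and the Discussion expects the study to show how determinants impact clinical outcomes and to inform the choice of implementation strategies. A predictor that is half post-treatment cannot carry that reading.

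**Working it through.** **Step 1. Share of the predictor rated after treatment.** Inputs are the stated wave timings. T1 is taken to precede the cases, and the four cases per practitioner are taken to be the families analysed.

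| Cases | Ratings before treatment | Ratings after treatment ended | Share after |
|---|---|---|---|
| 1-2 | T1 | T2, T3 | 2/3 |
| 3-4 | T1, T2 | T3 | 1/3 |

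Over four cases: (2 + 2 + 1 + 1) / 12 = 6/12 = one half. The case counts per wave are nominal, so the share will vary by practitioner. For the six-month outcome, a later rating may precede the assessment but still follows the end of treatment.

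**Step 2. Does the time-varying option avoid this?** The outcome is one change score per family, and no rule ties a survey wave to a family. For H2 the wording of that option also names implementation outcomes, not determinants. As written, it does not clearly cure the problem.

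**Step 3. How large could the effect be?** The protocol article gives no figure for H2 or H3 to reproduce, so this is an illustration. From the document: 44 practitioners and four cases each. Assumed: practitioner ICC of 0.05, a two-sided 5% test at practitioner level, ratings with half stable and half occasion variance (total 1), and feedback b, in SD of rating per SD of family outcome. Ratings have no effect on outcomes. T2 rises by b times the mean result of cases 1-2, and T3 by b times the mean result of cases 1-4.

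- Variance of the practitioner's mean outcome: V = 0.05 + 0.95/4 = 0.2875. The covariance between the mean of cases 1-2 and the mean of all four is also 0.2875. The variance of the mean of cases 1-2 is 0.05 + 0.95/2 = 0.525.
- Covariance of the three-wave mean with the outcome: (b/3)(V + V) = 2bV/3.
- Variance of the three-wave mean: 0.5 + 0.5/3 + (b²/9)(0.525 + 0.2875 + 2 × 0.2875) = 0.6667 + 0.1542b².
- At b = 0.4: covariance 0.0767, variance 0.6913, r = 0.0767 / √(0.6913 × 0.2875) = 0.172. Fisher's z times √41 is 1.11, so the chance of a significant result is P(Z > 1.96 − 1.11), about 20%.
- At b = 0.2: r = 0.087, about 9%. At b = 0.1: r = 0.044, about 6%.

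Simulation of this model (3,000 runs per setting) agrees:

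| b | T1-T3 mean, all cases | T1 only, all cases | T2, cases 3-4 only |
|---|---|---|---|
| 0 | 5.1% | 4.8% | 5.0% |
| 0.2 | 9.6% | 4.7% | 5.2% |
| 0.4 | 21.0% | 5.2% | 5.4% |
| 0.6 | 39.1% | 5.6% | 6.3% |
| 0.8 | 58.4% | 5.3% | 5.9% |

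**Step 4. Sensitivity to the model.** The rates depend heavily on two choices: whether b is scaled to a single family's result or to the practitioner's mean case result, and whether a shift in rating carries forward to the next wave. Across these versions, still at ICC 0.05, the three-wave mean gives about 6-8% at b = 0.1, 8-18% at b = 0.2 and 18-55% at b = 0.4. T1 alone stays at about 5% in all of them.

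**Step 5. Residue with T2.** For cases 3-4, T2 follows cases 1-2 of the same practitioner. At ICC 0 rejection is 4.4-5.1%. At ICC 0.10 it reaches at most 9.1%, at b = 0.8.

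**The case against.** The strongest reply is that H2 and H3 are worded as associations and the study describes itself as correlational. That stands. A reader might infer that the analysis cannot answer its hypotheses. The documents do not support this: an association that partly reflects reverse influence is still an association. What fails is the step from there to prediction or impact.

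Four further limits also stand.

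- A reader might take the three-wave mean to be the whole plan. It is one of two options, and the matching of waves to families under the other may be set out in a fuller document that is not shown.
- A reader might take H4 as evidence that the authors expect feedback from case results. H4 predicts a rise with experience over time. A uniform rise creates no association between practitioners' ratings and their families' outcomes. Feedback that depends on outcome is plausible but stated nowhere, so the predictor may contain the outcome; it is not shown to do so.
- A reader might extend the point to all of H3. Session-level fidelity is recorded during the family's own treatment, so the point reaches only AIM, IAM and FIM.
- The illustration models practitioners only. Around 80 leaders also supply ratings. They are not described as treating these families, and may show less feedback.

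**Conclusion.** The point holds for the mean option, for determinants in H2 and for AIM, IAM and FIM in H3. On the nominal schedule, half of the averaged predictor is rated after the family's treatment has ended, and nothing in the article restores the time order that H1 keeps. That count follows directly from the stated timings.

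The size of any resulting bias is not known. It rests on an assumed feedback strength, ICC and rating structure, and runs from almost nothing at b = 0.1 to a false-positive rate several times nominal at b = 0.4. No single rate from that range should be cited as the expected one. This should be corrected, since the remedy is cheap, but it does not invalidate the associational hypotheses.

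**What to change.** For H2, and for AIM, IAM and FIM in H3, state that the predictor is the most recent rating obtained before the family's pre-assessment: T1 for families starting before T2, and T2 for families starting after T2. Apply the rule under either predictor option. Keep the T1-T3 mean only as a descriptive sensitivity analysis, labelled as including post-treatment ratings. Exempt session-level FidQ data explicitly; a blanket ban on anything recorded after pre-assessment would remove the most direct test of fidelity against outcome.

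The cost is a change of wording and a date match between family start and survey wave. No new data are needed, and the article describes T3 as still to come. There are two downsides. One rating is noisier than a three-wave mean, so some precision is lost. Using T2 for later families also leaves the small residue through shared practitioner effects; an analysis with T1 alone for all families would show whether it matters.

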### Setting, participants, and recruitment

The study will be conducted in 24 municipalities, which vary in size, demography, and urbanicity and together represent all five health regions in Norway. Efforts are made to recruit heterogeneous municipalities, to reflect conditions as they are in the real world. The municipalities are part of an implementation network hosted by the Norwegian Center for Child Behavioral Development (NUBU; Norwegian acronym), and thus have some experience with implementation of EBIs [45]. Of the 24 municipalities, seven participated in co-creation of SPARCK [19].

Participants in the implementation study are SPARCK practitioners and municipal leaders. Currently, this includes 44 recruited practitioners, including 14 from the seven co-creation municipalities. In addition to training in SPARCK, all practitioners are trained in and actively practice Parent Management Training—Oregon model (PMTO) [45, 46]. Some are also trained in other EBIs. All practitioners are employed in municipal frontline mental health services, such as health care, school health services, and child welfare services. Participants also include the practitioners’ leaders, including their immediate manager, and superior leaders at mid and top managerial levels in the various services. Around 80 municipal leaders have so far been identified and recruited to the study. However, as staff turnovers are bound to happen, more will be recruited as needed. Written informed consent will be obtained from all participants before inclusion in the study.

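### Letting the estimated ICC and fit statistics decide whether design levels enter the model can make tests of cluster-shared predictors mildly too liberal, and the REML and FIML statements conflict where a predictor rating is missing

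*Protocol article*

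**What the plan says.** All statements on method are in the protocol article, Data analysis. The section recognises the nesting and commits to multilevel models in general, but adds that not every level is expected to matter and that "investigation of intraclass correlation coefficients (ICC) and design effects will guide our decisions regarding modeling". The two-level structure for H1 and the three-level structure for H2 and H3 are described as potential. The governing rule is that "complexity in the model is introduced only if the first steps in the model suggest it is necessary", with high ICCs and design effects given as examples. Model steps in all analyses are compared by -2LL, AIC and BIC.

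On estimation, maximum likelihood serves the model comparisons and "restricted maximum likelihood for final parameter estimates" follows. The next sentence reads "Missing data will be handled using full information maximum likelihood, in which all available data in the model contribute" to the parameters of the final model.

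The design is set out under Setting, participants, and recruitment: "The study will be conducted in 24 municipalities"; "Of the 24 municipalities, seven participated in co-creation of SPARCK"; "this includes 44 recruited practitioners, including 14 from the seven co-creation municipalities"; "Around 80 municipal leaders have so far been identified and recruited to the study". The same section expects staff turnover and further recruitment.

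**The concern.** There are two separate issues.

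**Clustering.** The levels are known from the design, but the default is to leave them out unless the data argue for them. With 24 small clusters the ICC is estimated poorly, and the design effect stays low even when clustering is real. If a real level is left out, standard errors are too small for predictors that members of a cluster share. These are co-creation status for staff, and a practitioner's or leader's rating when it predicts the outcomes of several families in H2 and H3.

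**Missing predictors.** A conditional mixed model fitted by REML uses incomplete outcomes under missing at random, but it cannot use a row whose predictor is missing. FIML covers missing predictors only if predictors and outcomes are modelled jointly, which is an ML model. H1 regresses T2 outcomes on T1 determinants, and staff recruited after T1 will have no T1 rating. The claim that all available data contribute therefore does not hold for such rows if REML gives the final estimates.

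**Working it through.** The article gives no ICC, threshold or sample size calculation, so there is no figure to reproduce. Assumptions: two-sided alpha 0.05, ICC 0.05 to 0.20, near-equal cluster sizes.

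**Cluster sizes.** Staff: (44 + 80)/24 = 124/24 = 5.17 per municipality. Practitioners: 44/24 = 1.83 per municipality. Families: four per practitioner by T3 (Study design and data collection).

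**Can the design effect look high?** DE = 1 + (m - 1) × ICC, so DE = 2 needs ICC = 1/(m - 1).
- Staff: 1/4.17 = 0.24.
- Families within practitioner: 1/3 = 0.33.
- Practitioners within municipality: 1/0.83 = 1.2, which is impossible.

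**Error if the level is left out.** For a predictor constant within the cluster, type I error = 2 × [1 - Φ(1.96/√DE)]. Example, staff at ICC 0.10: DE = 1 + 4.17 × 0.10 = 1.417, and 1.96/√1.417 = 1.647, giving 10.0%.

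| Level omitted, shared predictor | ICC 0.05 | ICC 0.10 | ICC 0.20 |
|---|---|---|---|
| Staff in municipality (m = 5.17) | 7.5% | 10.0% | 14.8% |
| Practitioners in municipality (m = 1.83) | 5.5% | 6.0% | 7.0% |
| Families sharing a practitioner (m = 4) | 6.8% | 8.6% | 12.1% |

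For an individual-level H1 slope, DE = 1 + (m - 1) × ICCx × ICCy. At ICCx 0.2 and ICCy 0.1, DE = 1 + 4.17 × 0.02 = 1.083 and the error is 6.0%. At 0.4 and 0.2, DE = 1.333 and the error is 9.0%.

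**Error of the whole keep-or-drop procedure.** These are simulations under the null for 7 against 17 municipalities with about 5 staff each. The level is kept or dropped on the intercept-only model. If it is dropped, a person-level t test is used; if kept, a t test on municipality means with 24 - 2 = 22 df. The Monte Carlo standard error is about 0.2 to 0.3 percentage points.

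| Rule for keeping the municipality level | Type I error, ICC 0.05 to 0.20 |
|---|---|
| AIC (named) | 5.4% to 6.1% |
| -2LL, chi-square on 1 df (named; cutoff assumed) | 6.3% to 7.3% |
| BIC (named) | 6.8% to 7.8% |
| Drop if DE < 2 (assumed cutoff) | 7.3%, 9.6%, 10.4% at 0.05, 0.10, 0.20 |
| Drop if F test not significant (assumed) | 5.9%, 6.2%, 5.8% |
| Drop if ICC < 0.05 (assumed) | 4.7%, 5.0%, 5.2% |
| Always kept | 4.8% to 5.2% |

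Real clustering is often missed. At ICC 0.10 the level is dropped in 96% of data sets under DE < 2 and in 58% under the F test.

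**Missing predictors.** The share of staff without a T1 rating is an assumption. Rows lost = 124 × share, and the standard error grows by 1/√(1 - share).
- 10%: 12.4 rows, factor 1.05.
- 20%: 24.8 rows, factor 1.12.
- 30%: 37.2 rows, factor 1.20.

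**The case against.** The strongest reply is that the article states no cutoff. It says nesting must be accounted for or modelled, it commits to multilevel models, and ICC and design effect only guide the choice. A reader might infer that municipality-level tests will run at 10% or more. The documents do not support that: it needs a design effect cutoff of 2, which appears nowhere. Under the fit criteria that are named the error is below 8%, and under a strict ICC rule there is essentially no inflation. This part of the objection stands.

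It also stands that the 7 against 17 contrast is exploratory, and that H1 slopes and practitioner-only outcomes such as fidelity inflate less. The contrast is planned for readiness and implementation outcomes, so it should not be carried over to the clinical outcomes of families.

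On missing data, a reader might infer that staff will be lost unnoticed, or that one missed wave removes a family from H2 or H3. Neither follows. The article does not say that the T1 to T3 mean needs all three waves, and it offers a time-varying covariate as an alternative. If a joint ML model is fitted, no rows are lost and it is the REML sentence that is wrong. The time effect in H4 and co-creation status have no missing predictor. Rows without the predictor also add little to a slope unless auxiliary variables are used, so the cost is mainly precision and possible selection by turnover.

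Finally, cutoffs and degrees-of-freedom methods are often left to an analysis plan. Their absence is not the point here. The conditional inclusion of design levels and the REML/FIML pair are both stated.

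**Conclusion.** The point holds in a moderate form. The stated rule lets noisy estimates remove levels known from the design, and tests of cluster-shared predictors can then be too liberal. For the 7 against 17 contrast the size is about 5.4% to 8% under the named criteria, about 10% at most under the assumed design effect cutoff, and little or nothing under a strict ICC rule. This rests on assumed ICCs of 0.05 to 0.20 and near-equal clusters. For rater-level predictors of family outcomes only the error with the practitioner level omitted was computed (6.8% to 12.1%); the keep-or-drop procedure was not simulated there.

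The REML and FIML sentences are inconsistent for H1 to H3 wherever a predictor rating is missing, which expected turnover makes likely. The loss of 12 to 37 of 124 rows in H1 depends on the assumed 10% to 30% missingness and on REML being the method that governs.

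**What to change.** **Clustering.** Keep a municipality random intercept in every model, and a practitioner intercept for family outcomes in H2 and H3, whatever the estimated ICC. Fit by REML with Kenward-Roger or Satterthwaite degrees of freedom. Reserve AIC, BIC and -2LL for adding random slopes or other complexity. With 1.83 practitioners per municipality some variances may be hard to separate, so state in advance that cluster-robust inference with a small-sample correction will be used if a variance is estimated at zero or the fit is singular.

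**Missing predictors.** Replace the REML/FIML pair with one coherent method. Either fit a joint ML model of predictors and outcomes, or use multilevel multiple imputation followed by the REML model in each imputed data set. Limit either to staff who were in post at T1, since a T1 rating has no clear meaning for someone who joined later.

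**Cost.** A change of wording and some programming, with slightly wider intervals when the true ICC is near zero. No data collection changes.
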